### Statistical analysis

2.9

#### Analysis populations

2.9.1

The analysis populations will consist of the full analysis set (FAS) and the per protocol set (PPS). The FAS will include all randomized participants who receive at least one application of the investigational device and have at least one post-baseline assessment and will be used for primary efficacy analyses in accordance with the intention-to-treat (ITT) principle. The PPS will include participants without major protocol deviations and with a treatment compliance rate of at least 70% and will be used for supportive analyses.

Missing data will be handled within the LMM and generalized linear mixed-effects model (GLMM) using maximum likelihood estimation under the missing-at-random assumption, which allows valid inference without explicit imputation.

In addition, sensitivity analyses will be conducted using multiple imputation to assess the robustness of the results to different missing data assumptions.

No interim analyses are planned.

#### Demographic data and baseline clinical characteristics

2.9.2

Demographic variables will include age, height, weight, smoking status, alcohol consumption, physical activity, and educational level. Baseline clinical characteristics will include relevant medical history, concomitant medications, baseline VAS scores, and vital signs.

Continuous variables will be summarized as mean ± standard deviation, and categorical variables will be summarized as frequencies and percentages. Between-group comparisons will be performed using the independent *t*-test or Wilcoxon rank-sum test, depending on the distribution of the data. Categorical variables will be compared using the chi-square test or Fisher’s exact test, as appropriate.

#### Between-group comparisons

2.9.3

The primary endpoint, defined as the change from baseline in the VAS measured at the scheduled post-menstrual visit occurring within days 1–3 after menstruation onset, will be analyzed using an LMM. Fixed effects will include treatment group, visit (time point), and the group-by-visit interaction, with baseline VAS included as a covariate. Analgesic use will also be included as a covariate to adjust for its potential confounding effect on pain outcomes. Analgesic exposure in the primary analysis will be defined based on use within a predefined time window prior to VAS assessment. Cumulative analgesic use during the assessment period will be considered in sensitivity analyses. Participant-level variability will be modeled as a random effect.

For secondary outcomes, continuous variables, such as biosignal measures and patient-reported outcomes, will be analyzed using LMMs, and binary or ordinal outcomes, such as PGIC, will be analyzed using the generalized linear mixed-effects models (GLMMs), with treatment group, visit, and group-by-visit interaction specified as fixed effects and participant-level variability as a random effect.

Biosignal analyses will be conducted as exploratory outcomes, and the findings will be interpreted as hypothesis-generating.

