#### Analgesic handling

2.3.4

The use of rescue analgesics (such as NSAIDs) will be permitted as needed and will be systematically recorded, including timing, frequency, and dosage. Analgesic use within a predefined time window prior to VAS assessment will be included as a covariate in the primary analysis to account for its potential immediate effect on pain reporting.

All medication use will be recorded throughout the study period. In addition, cumulative analgesic use during the assessment period will be considered in sensitivity analyses.

Participants will be instructed to refrain from receiving other treatments for dysmenorrhea, including additional light therapy, transcutaneous electrical nerve stimulation, acupuncture, or other physical or complementary therapies, during the trial period.

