#### Primary outcome

2.8.1

The primary outcome is the change from baseline in menstrual pain intensity measured using a 0–100-mm VAS (26). The primary endpoint is defined as the change from baseline in VAS measured at the scheduled post-menstrual visit occurring within 3 days after the onset of menstruation, assessed across three menstrual cycles.

A visit window of up to 3 days after menstruation onset is allowed to accommodate inter-individual variability in the timing of peak pain and to ensure feasibility while minimizing protocol deviations. Assessments will be conducted at baseline and at each post-menstrual visit (visit window: day 1 + 3 days) over three menstrual cycles.

To further characterize individual pain patterns, VAS scores will be recorded daily from 7 days prior to menstruation through the first 3 days of menstruation. Sensitivity analyses will be conducted using alternative outcome definitions, including the maximum VAS during menstrual days 1–3.

To evaluate treatment effects, a linear mixed-effects model (LMM) will be used, with treatment group, visit (time point), and group-by-visit interaction specified as fixed effects, and participant-level variability included as a random effect. Baseline VAS will be included as a covariate (27).

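### The primary VAS model adjusts for as-needed analgesic use after randomisation, so the group coefficient is in general neither the intention-to-treat difference nor the difference without analgesics

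*Protocol article*

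**What the plan says.** On the outcome, section 2.8.1 of the protocol article states: "The primary endpoint is defined as the change from baseline in VAS measured at the scheduled post-menstrual visit occurring within 3 days after the onset". The onset meant is that of the menses, and three cycles are covered. The same section gives the mixed model as group, visit, group-by-visit interaction and a participant random effect, and names baseline VAS as the only covariate.

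On analgesics, section 2.3.4 states: "The use of rescue analgesics (such as NSAIDs) will be permitted as needed and will be systematically recorded, including timing, frequency, and dosage". It then says: "Analgesic use within a predefined time window prior to VAS assessment will be included as a covariate in the primary analysis". The reason given there is the immediate effect of an analgesic on pain reporting.

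Section 2.9.3 repeats the model with baseline VAS and adds: "Analgesic use will also be included as a covariate to adjust for its potential confounding effect on pain outcomes". It continues: "Analgesic exposure in the primary analysis will be defined based on use within a predefined time window prior to VAS assessment". For sensitivity analyses it says: "Cumulative analgesic use during the assessment period will be considered in sensitivity analyses".

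Three other places matter. Table 1 puts randomisation at Visit 1 and the outcome VAS at Visits 2 to 4. Section 2.6 says participants cannot be blinded. Section 2.9.1 says the primary analysis follows the intention-to-treat principle.

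**The concern.** A confounder of the group effect must influence allocation or share a cause with it. Allocation is random and happens at Visit 1, so analgesic use before Visits 2 to 4 can do neither. It is an intercurrent event that lies downstream of pain, and possibly of allocation through expectation.

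Conditioning on it does two things. It removes any part of the group difference in VAS that arises because one arm needs fewer analgesics. It also compares women who are no longer alike: if one site lowers pain, the women there who still take an analgesic are selected for having had more pain to begin with.

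Section 2.7 says the preliminary effect estimate will inform the sample size of a confirmatory trial. Required size varies with 1/effect² at a fixed SD. An effect understated by 33% would multiply that size by 1/0.67² = 2.2; one overstated by 29% would multiply it by 1/1.29² = 0.60.

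**Working it through.** The plan gives no figure to reproduce here: it states no effect size, SD, analgesic effect or rate of use. The check is therefore structural, followed by simulation on assumed inputs.

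**Step 1. Timing.** Randomisation is at Visit 1 (Table 1). The covariate is use in a window before each VAS (2.9.3), and the outcome VAS is taken at Visits 2 to 4. The covariate is therefore measured after randomisation, and as-needed use (2.3.4) makes it depend on pain.

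**Step 2. Where the error comes from.** In a linear model with the same other terms,

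total difference = adjusted difference + b × d,

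where b is the fitted analgesic coefficient and d is the between-arm difference in the proportion using analgesics. The error, adjusted minus total, is −b × d. It vanishes if d = 0. Its sign depends on b, which mixes two opposing things: use marks severe pain (pushes b up), and the drug lowers pain (pushes b down).

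**Step 3. Three-visit random-intercept model with baseline VAS.** Assumed: between-person SD 15 mm, within-person SD 12 mm, measurement SD 8 mm, 50% use in the reference arm, logit slope of use on pain 0.10 or 0.05 per mm, and a 10 mm group difference in pain before analgesic. Figures are mm of benefit; 200,000 simulated participants per row.

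| Slope | Analgesic effect | Total | Adjusted | b | Error |
|---|---|---|---|---|---|
| 0.10 | 0 | 10.09 | 7.82 | +14.90 | −2.27 (−22%) |
| 0.10 | 10 | 8.48 | 7.72 | +4.92 | −0.76 (−9%) |
| 0.10 | 20 | 6.96 | 7.73 | −5.12 | +0.77 (+11%) |
| 0.10 | 30 | 5.41 | 7.72 | −15.06 | +2.31 (+43%) |
| 0.05 | 0 | 9.98 | 9.05 | +8.84 | −0.93 (−9%) |
| 0.05 | 10 | 9.03 | 9.16 | −1.22 | +0.13 (+1%) |
| 0.05 | 20 | 7.83 | 8.98 | −11.08 | +1.15 (+15%) |
| 0.05 | 30 | 6.92 | 9.10 | −21.25 | +2.18 (+32%) |

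The identity checks. In row 2, use is 50% against 35%, so d = −0.15. On the VAS scale, −7.72 + 4.92 × (−0.15) = −8.46, against −8.48 simulated. In that row b is positive although the assumed drug lowers VAS by 10 mm.

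The adjusted value also misses the 10 mm difference without analgesics in every row, by about 0.8 to 2.3 mm. With no group effect on pain or on use, both models give about 0.

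**Step 4. Single-visit model with baseline VAS.** Assumed: mean 55 mm, between-person SD 15 mm, within-person SD 13.2 mm (total √(15² + 13.2²) ≈ 20 mm), use logistic in pain with scale 8 or 15 mm, and the same 10 mm difference.

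| Analgesic effect | Total (scale 8; 15) | Adjusted (scale 8; 15) | Error |
|---|---|---|---|
| 0 | 10.0; 10.0 | 6.7; 8.2 | −33%; −18% |
| 10 | 8.4; 8.8 | 6.7; 8.2 | −20%; −7% |
| 20 | 6.8; 7.6 | 6.7; 8.2 | −2%; +8% |
| 30 | 5.2; 6.3 | 6.7; 8.2 | about +29% in both |

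**Step 5. The two descriptions of the model.** Section 2.8.1 has baseline VAS alone; 2.9.3 has baseline VAS plus analgesic use. Both describe the primary analysis.

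**The case against.** The strongest defence is the purpose given in 2.3.4: a recent analgesic can mask pain, and the investigators want pain unmasked. That is a legitimate question. With a 20 or 30 mm analgesic effect and slope 0.10, the adjusted 7.7 mm is nearer to the 10 mm pain difference than the unadjusted 7.0 or 5.4 mm. What stands is that the unadjusted difference is a choice of estimand and not the only defensible one. What does not stand is that a plain covariate answers the question: it missed 10 mm in every row. The plan also claims intention-to-treat, which points to the total difference.

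Second, this is a pilot with no powered test. Under the step 3 SDs with no analgesic effect, the residual variance of a three-visit mean given baseline is 225 + (144 + 64)/3 − 225²/369 = 157. The standard error of the difference is then √(2 × 157/30) = 3.2 mm, or √(2 × 157/24) = 3.6 mm after 20% dropout. Both exceed the largest error in step 3 (2.3 mm). That is fair, but the error is avoidable and would be carried into the next trial's design.

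A reader might infer more than the article supports:

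- *That an effective site will look less effective.* The tables show error in both directions.
- *That no planned analysis gives the total difference.* Section 2.8.1 names only baseline VAS, and its sensitivity analysis on maximum VAS mentions no analgesic term. The text is inconsistent on this, not silent.
- *That the sensitivity analysis adjusts for cumulative use.* The article says only that such use will be considered.
- *That the unstated window length is a defect.* A condensed article may leave it to the full protocol.

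**Conclusion.** The point holds. The primary model in 2.3.4 and 2.9.3 conditions on a post-randomisation, pain-driven variable under a confounding rationale that does not apply to a randomised comparison. When the arms differ in pain or in analgesic use, the coefficient generally estimates neither the intention-to-treat difference nor the analgesic-free one.

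Size and sign cannot be obtained from the documents. For a 10 mm pain difference, the single-visit assumptions give about 33% attenuation to about 29% inflation, and the three-visit assumptions give about 22% attenuation to about 43% inflation. Some combinations nearly cancel, and there is no error if the arms differ in neither pain nor use. All of these figures rest on assumed SDs, analgesic effects and rates of use.

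Separately, 2.8.1 and 2.9.3 disagree on the covariates. The only analgesic-related sensitivity analysis named uses cumulative use, which is also post-randomisation, so it would not serve as a check on this choice.

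**What to change.** 1. Remove analgesic use from the primary mixed model in 2.3.4 and 2.9.3, so that both match 2.8.1: group, visit, group-by-visit, baseline VAS and participant random effect. Drop the reference to confounding.
2. State that the primary estimate is the difference in VAS regardless of analgesic use.
3. Report analgesic use by arm (timing, frequency and dosage are already recorded) beside the VAS result.
4. Keep models adjusted for analgesic use, in the window or cumulative, only as supplementary analyses labelled as non-randomised comparisons.

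The cost is wording in two sections and in the analysis plan; no new data are needed. Section 2.2 schedules recruitment to October 2026 and analysis into 2027, so on that timetable the change can precede analysis. The downside is real: the VAS difference must be read together with analgesic use, because a recent analgesic can mask part of a pain difference.

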Medical and treatment history (including medication use)	●							
Physical examination	●							
Vital signs	●	●		●		●		●
Anthropometrics	●							
Laboratory tests (blood)^a^	●							
Pregnancy test	●							
Visual analog scale (VAS) for pain	●	●		●		●		●
Beck Depression Inventory-II (K-BDI-II)	●	●		●		●		●
Inclusion/exclusion criteria	●							
Allocation								
Randomization		●						
Intervention^b^								
Home-based LLLT at local acupoint (self-administration, daily for 7 days premenstrual)			●		●		●	
On-site LLLT at local acupoint				●		●		●
Home-based LLLT at distal acupoint (self-administration, daily for 7 days premenstrual)			●		●		●	
On-site LLLT at distal acupoint				●		●		●
Assessment								
Quality of life (EQ-5D-5L)		●		●		●		●
Stress response inventory-short form (SRI-SF)		●		●		●		●
State–trait anxiety inventory (STAI)		●		●		●		●
Device dispensing and training for home-based self-administration		●						
Clinical device return								●
Analgesic use check (type and dose)		●		●		●		●
Menstrual diary (distribution/collection)		●		●		●		●
Multimodal biosignal measurements^c^				●		●		●
Compliance with home-based LLLT				●		●		●
Patient Global Impression of Change (PGIC)								●
Changes in medical/treatment history		●		●		●		●
Adverse events				●		●		●
End of study/case closure								●

^a^If laboratory test results within 2 weeks prior to screening are available, they may be used in place of repeat testing at screening. Tests include complete blood count (CBC), liver function tests [such as total bilirubin, total protein, albumin, aspartate transaminase (AST), alanine transaminase (ALT), alkaline phosphatase (ALP), and gamma-glutamyl transferase (GGT)], renal function (such as BUN and creatinine), thyroid function (TSH), and HbA1c. ^b^Low-level light therapy will be performed as home-based self-administration once daily for 20 min during the 7 days prior to menstruation, followed by a single on-site supervised session at each cycle visit. Participants will record light therapy adherence and pain levels in the provided diary. ^c^Multimodal biosignal measurements (on-site only: pre−/during/post-stimulation). Biosignal monitoring will include six parameters: respiration (RSP), electrocardiogram (ECG), photoplethysmography (PPG), electrodermal activity (EDA), skin temperature (SKT), and electromyography (EMG). SPIRIT, Standard Protocol Items: Recommendations for Interventional Trials.

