### Sample size

2.7

As this study is an exploratory pilot trial, the sample size was determined primarily based on feasibility considerations and the need to obtain preliminary estimates for a future confirmatory randomized controlled trial, rather than to test a definitive efficacy hypothesis. We therefore did not base the sample size on a formal power calculation. A total of 60 participants, with 30 participants per group, was considered appropriate for evaluating key feasibility parameters, including recruitment, adherence, retention, safety, and completion of outcome assessments. This sample size was also expected to provide preliminary estimates of treatment effect and variability, which will be used to inform the design and sample size calculation of a future adequately powered confirmatory trial. Allowing for an anticipated dropout rate of approximately 20%, the target enrollment was set at 60 participants in total.

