#### Secondary outcomes

2.8.2

The secondary outcomes include changes in biosignals and patient-reported outcomes, such as the Korean version of the Beck Depression Inventory-II (K-BDI-II) (28), the EuroQol 5-Dimension 5-Level (EQ-5D-5L) (29), the Stress Response Inventory-Short Form (SRI-SF) (30, 31), and the State–Trait Anxiety Inventory (STAI) (32) assessed at baseline and at each post-menstrual visit (visit window: day 1 + 3 days) over three cycles. PGIC will be assessed once at the final visit (33).

Multimodal biosignals: Multimodal biosignals will be acquired at baseline and at each post-menstrual visit over three menstrual cycles, including RSP, ECG, PPG, EDA, SKT, and EMG. Biosignal measurements will be analyzed as exploratory outcomes. The underlying hypothesis is that stimulation at different acupoint locations may induce differential modulation of physiological responses. Given the exploratory nature of these analyses, no formal adjustment for multiple comparisons will be applied, and the findings will be interpreted as hypothesis-generating.

K-BDI-II: The K-BDI-II is the validated Korean translation of the Beck Depression Inventory-II, a widely used self-reported measure of depressive symptoms. It consists of 21 items, each scored on a 4-point Likert scale (0–3), reflecting symptom severity over the past 2 weeks. Total scores range from 0 to 63, with higher scores indicating more severe depressive symptoms. Standard cutoff scores are defined as minimal (0–13), mild (14–19), moderate (20–28), and severe (29–63).

EQ-5D-5L: The EQ-5D-5L is a standardized instrument for assessing health-related quality of life. It comprises five dimensions: mobility, self-care, usual activities, pain/discomfort, and anxiety/depression. Each dimension is rated on five levels (from no problems to extreme problems). Responses are converted into a single index score using country-specific value sets, with higher scores indicating better health status. In addition, the EQ-5D-5L includes a visual analog scale (VAS; 0–100) for self-rated overall health.

SRI-SF: The SRI-SF is a validated short-form instrument used to assess multidimensional stress responses. It consists of 22 items scored on a 5-point Likert scale (0–4), covering emotional, somatic, cognitive, and behavioral domains. Total scores range from 0 to 88, with higher scores indicating greater stress response levels.

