STAI: The STAI is a self-report measure used to evaluate anxiety. It consists of 40 items divided into two subscales: state anxiety (20 items), assessing transient anxiety, and trait anxiety (20 items), measuring general anxiety disposition. Each item is rated on a 4-point Likert scale, with subscale scores ranging from 20 to 80. Higher scores indicate greater levels of anxiety.

PGIC: The PGIC is a single-item measure assessing a patient’s overall perception of change following treatment. It is rated on a 7-point Likert scale ranging from 1 (significantly improved) to 7 (worse response). It is widely used as a global measure of perceived treatment effectiveness.

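### PGIC is measured once, at Visit 4, but section 2.9.3 assigns it a repeated-measures mixed model whose visit terms cannot be estimated and whose random effect has nothing sound to rest on

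*Protocol article*

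**What the plan says.** Section 2.8.2 of the protocol article fixes the timing: "PGIC will be assessed once at the final visit". Table 1 agrees, since the row "Patient Global Impression of Change (PGIC" carries a single mark in the close-out column, Visit 4. The same section describes the scale: "It is rated on a 7-point Likert scale ranging from 1 (significantly improved) to 7 (worse response". The item is itself a rating of change, so it has no baseline value.

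Section 2.9.3 gives the analysis: "binary or ordinal outcomes, such as PGIC, will be analyzed using the generalized linear mixed-effects models (GLMMs), with treatment group, visit, and group-by-visit interaction" are "specified as fixed effects and participant-level variability as a random effect". PGIC is the only binary or ordinal secondary outcome named for this model. No other section gives PGIC a single-time-point analysis. The rank-sum, chi-square and exact tests in section 2.9.2 are for demographic and baseline characteristics.

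On missing data, section 2.9.1 relies on maximum likelihood within the mixed models under missing at random, "which allows valid inference without explicit imputation", and adds multiple imputation as a sensitivity analysis.

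**The concern.** Visit, group-by-visit and a participant random effect describe an outcome observed several times on each woman. PGIC is observed once. The model named for it therefore conflicts with the trial's own schedule. This is a stated analysis that does not fit its outcome, so it is not a detail left to an unseen analysis plan.

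The analyst will have to depart from the article. Software may drop the redundant terms, fail, or return a group effect whose scale depends on a variance that the data do not determine. Section 2.7 says the trial should supply preliminary effect estimates for a confirmatory trial. A PGIC odds ratio on an undetermined scale would not serve that purpose.

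**Working it through.** The article states no figure on this point, so there is none to reproduce. The check concerns the structure of the model.

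**Inputs from the article**
- One PGIC value per woman, at Visit 4 (section 2.8.2, Table 1).
- Two groups of 30 (section 2.7: "A total of 60 participants, with 30 participants per group, was considered appropriate for evaluating key feasibility parameters").
- Fixed effects group, visit and group-by-visit, and a participant random effect (section 2.9.3).

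**Assumed for illustration only**
- Binary version: 12/30 against 18/30 responders.
- Seven-level version: counts 2, 5, 8, 8, 4, 2, 1 against 4, 8, 8, 6, 2, 1, 1.
- Random-intercept SD set at 0, 0.5, 1, 2 and 3.

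**Step 1: fixed effects.** For three post-baseline visits with Visit 2 as reference, the columns are intercept, group, V3, V4, group×V3 and group×V4. If every row is at Visit 4, then V3 = 0, V4 = intercept, group×V3 = 0 and group×V4 = group. Only intercept and group remain distinct.
- Visit 4 only: 6 columns, rank 2.
- Three visits: 6 columns, rank 6.

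So 6 − 2 = 4 columns, all the visit and group-by-visit terms, cannot be estimated. This does not depend on the sample size or the responses.

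**Step 2: random effect, binary outcome.** With one response per woman, the likelihood depends only on the marginal response probability in each group. For any SD, the two coefficients can be chosen to reproduce 12/30 and 18/30 exactly, so the maximised log-likelihood is always

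2 × [12 ln(0.4) + 18 ln(0.6)] = −40.3807.

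The profile calculation gives this value at every SD from 0 to 3, under both links. The group coefficient is not constant:

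| SD | logit | probit |
|---|---|---|
| 0 | 0.811 | 0.507 |
| 1 | 0.980 | 0.717 |
| 2 | 1.336 | 1.133 |
| 3 | 1.761 | 1.602 |

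The probit column follows β₀ × √(1 + SD²); for example, 0.507 × √2 = 0.717. The variance is not identified.

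**Step 3: random effect, seven-level outcome.**

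| SD | logit log-likelihood | logit coefficient | probit log-likelihood | probit coefficient |
|---|---|---|---|---|
| 0 | −103.6350 | 0.714 | −103.7582 | 0.392 |
| 1 | −103.6706 | 0.824 | −103.7582 | 0.554 |
| 2 | −103.7220 | 1.068 | −103.7582 | 0.876 |
| 3 | −103.7441 | 1.379 | −103.7582 | 1.238 |

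Under probit the likelihood is flat again. Under cumulative logit it moves by 103.7441 − 103.6350 = 0.11, while the odds ratio moves from exp(0.714) = 2.04 to exp(1.379) = 3.97. That small movement comes only from the difference in shape between a logistic and a normal-mixed logistic distribution. It carries no information on variation between women.

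**Step 4: after correction.** With visit, interaction and random effect removed, thresholds plus group are estimable from one row per woman. In the assumed example, the proportional-odds log odds ratio is 0.71.

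**The case against.** The strongest reply is that this is a drafting slip. One sentence was written to cover all binary and ordinal outcomes, and once the terms that mean nothing at a single visit are dropped, the intended group comparison at Visit 4 remains. That stands as a limit on severity, and the rank of 2 confirms it. It does not remove the contradiction, because PGIC is the named example and no alternative is given.

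Several stronger readings are tempting, and the documents do not support them.

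- **The model cannot be fitted at all.** This is strictly true of visit and group-by-visit, and the variance is not identified for a binary outcome or a probit link. Under a cumulative logit, software may return an answer. In the assumed example above, the likelihood is highest at an SD of 0, the ordinary proportional-odds fit.
- **The odds ratio is inflated by a known amount.** Any percentage needs a random-effect SD, and the article gives none. The figures above show sensitivity and do not predict a bias.
- **Missing-data handling fails for PGIC.** With one response per woman, likelihood inference on the observed values is still valid if missingness depends only on terms in the model. What is lost is support from earlier PGIC values. Section 2.9.1 also plans multiple imputation.
- **Dropout losses are caused by this model.** The anticipated 20% dropout would be 0.20 × 60 = 12 women, but any outcome taken only at Visit 4 loses them, under the corrected model too.
- **The replacement will be picked after seeing results.** An analysis plan may exist that settles it, and section 2.6 has the analysis run on blinded group codes.

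**Conclusion.** The point holds. The schedule gives PGIC one assessment, and section 2.9.3 assigns it a model that needs repeated assessments. All four visit and interaction columns are inestimable. The random-effect variance is either unidentified (binary outcome or probit link) or rests on link shape alone (cumulative logit), which leaves the scale of the group odds ratio arbitrary. The fixed-effect result rests only on the schedule and the stated model. The coefficients in steps 2 and 3 rest on assumed response counts and illustrate the problem without measuring it.

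Severity is moderate to minor. PGIC is a secondary, single-item outcome in a pilot that disclaims definitive efficacy testing. The primary VAS analysis has three post-baseline visits and is unaffected. A reader might infer that the trial's conclusions are at risk, but nothing in the article makes them depend on PGIC.

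**What to change.** In section 2.9.3, and in the analysis plan if there is one:

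1. Analyse PGIC at Visit 4 with a proportional-odds logistic regression with group as the effect, without visit, interaction or random effect. Report a common odds ratio with 95% CI, and state its direction, since low scores are favourable. Baseline VAS may be added as a covariate; this is optional, because the article does not list it for secondary outcomes.
2. Limit the generalized linear mixed model to binary or ordinal outcomes measured at more than one visit.
3. In the multiple imputation already planned in section 2.9.1, impute PGIC from group, baseline VAS and the VAS values observed before dropout. A woman who misses Visit 4 will normally lack the Visit 4 VAS as well, so the imputation should not depend on it.

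The cost is a sentence or two of text. Data collection, visits and sample size do not change.

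### The secondary-outcome models in section 2.9.3 list no baseline covariate for the questionnaires, although the baseline values are collected and the primary model has one

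*Protocol article*

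**What the plan says.** Section 2.9.3 (Between-group comparisons) sets out two models in consecutive paragraphs. For the primary endpoint: "Fixed effects will include treatment group, visit (time point), and the group-by-visit interaction, with baseline VAS included as a covariate". Section 2.8.1 repeats this: "Baseline VAS will be included as a covariate". For the secondary outcomes, the LMMs and GLMMs are given "with treatment group, visit, and group-by-visit interaction specified as fixed effects and participant-level variability as a random effect", and no baseline term is listed.

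Section 2.8.2 describes the response in terms of change, "The secondary outcomes include changes in biosignals and patient-reported outcomes", and has the questionnaires "assessed at baseline and at each post-menstrual visit (visit window: day 1 + 3 days) over three cycles". Section 2.9.3 does not say whether the modelled response is the change or the raw score.

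Table 1 (section 2.2) marks EQ-5D-5L, SRI-SF and STAI at Visit 1 and K-BDI-II at Visits 0 and 1, all before the first self-treatment. Randomisation is also marked at Visit 1, and section 2.6 states that it is unstratified.

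**The concern.** A baseline term is named for one model and absent from the listed terms of the next, with no reason given for treating the questionnaires differently from the VAS. A statistician who followed the list would fit no baseline covariate.

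The participant random effect does not take its place. It accounts for correlation within a woman, but it does not remove between-woman variation from a comparison of parallel groups.

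Two things are at stake for K-BDI-II, EQ-5D-5L, SRI-SF and STAI. The first is precision: section 2.7 says the trial is meant to supply preliminary estimates of effect and variability for a later trial. The second is the handling of chance baseline differences in a small, unstratified sample.

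**Working it through.** **Inputs from the protocol.** Section 2.7: "A total of 60 participants, with 30 participants per group, was considered appropriate for evaluating key feasibility parameters". The same section anticipates about 20% dropout: 60 × 0.8 = 48, or 24 per arm. It gives no alpha, power, effect size or SD, so there is no figure of the plan's own to reproduce.

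**Assumptions.** Equal variance at all visits (SD = 1), and the same correlation r between any two visits. The protocol gives no correlation, so r = 0.3, 0.5, 0.7 and 0.8 are shown.

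**Precision at a single visit.** Per-woman variance feeding the group difference:

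- raw follow-up score: 1
- change score: 2(1 − r)
- baseline as covariate: 1 − r²

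Covariate relative to change score: (1 − r²) / [2(1 − r)] = (1 + r)/2. Covariate relative to raw score: 1 − r².

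| r | ratio to change score | variance cut | ratio to raw score | variance cut |
|---|---|---|---|---|
| 0.3 | 0.65 | 35% | 0.91 | 9% |
| 0.5 | 0.75 | 25% | 0.75 | 25% |
| 0.7 | 0.85 | 15% | 0.51 | 49% |
| 0.8 | 0.90 | 10% | 0.36 | 64% |

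The SE is √(2v/n). At r = 0.5 and 30 per arm, it is √(2 × 1/30) = 0.258 SD for either unadjusted form and √(2 × 0.75/30) = 0.224 SD with the covariate.

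**Baseline as a level of visit.** Random-intercept models were fitted to simulated complete data (30 per arm, 150 runs each at r = 0.5 and 0.7). The group-by-visit contrast at Visit 4 matched the change-score contrast to machine precision (largest difference about 3 × 10⁻¹⁵). With complete data this reading therefore has the change-score column's loss. Simulated SEs for visit level and covariate were 0.243 and 0.204 at r = 0.5, and 0.197 and 0.187 at r = 0.7.

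**Mean of the three follow-up visits.** The variances are (1 + 2r)/3 for raw, (1 + 2r)/3 + 1 − 2r for change, and (1 + 2r)/3 − r² with the covariate. In order of r, the covariate ratios are 0.48, 0.63, 0.78 and 0.85 to change, and 0.83, 0.63, 0.39 and 0.26 to raw.

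**Chance imbalance.** The SD of the baseline group difference is √(2/30) = 0.258 SD, or √(2/24) = 0.289 SD at 24 per arm. The chance that it exceeds 0.3 SD in either direction on one scale is 2[1 − Φ(0.3/0.258)] = 0.245, or 0.299 at 24 per arm. Given a 0.3 SD imbalance, the expected error is 0.3r for raw scores and 0.3(r − 1) for change scores:

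| r | raw score | change score |
|---|---|---|
| 0.3 | +0.09 | −0.21 |
| 0.5 | +0.15 | −0.15 |
| 0.7 | +0.21 | −0.09 |
| 0.8 | +0.24 | −0.06 |

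Raw scores leave the imbalance in and change scores over-correct it. With baseline as a covariate, modelling the raw or the change score gives the same group contrasts.

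**The case against.** The best counter-argument is that the secondary sentence is a family description and not a literal model. It covers biosignals, questionnaires and PGIC together. Read literally, it gives PGIC a visit effect and an interaction, yet "PGIC will be assessed once at the final visit". A baseline term could not be common to all these outcomes, and outcome-specific covariates may sit in a document not shown. This lowers certainty about what will be fitted. It does not supply a baseline covariate anywhere, and the contrast with the preceding paragraph remains.

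The second argument is that section 2.8.2 speaks of changes, so baseline is probably not discarded. This stands, and it rules out some stronger readings:

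- A reader might infer that all between-woman variance stays in the comparison, or that adjustment would make 60 women worth 80 to 118 (60/0.75 and 60/0.51). Those figures belong to the raw-score reading, which the text supports less well. At high correlation the gain over change scores is modest.
- A reader might infer that the questionnaire results will be biased. Randomisation keeps them unbiased on average under every reading; any error is conditional on the imbalance that occurs.
- A reader might infer that material imbalance is likely. On any one scale, a difference above 0.3 SD has a chance of about 24 to 30%.

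Finally, these are secondary outcomes of a pilot with no formal power calculation, and the primary outcome is already adjusted. That limits the consequence but gives no reason to forgo the gain.

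**Conclusion.** The point holds as a matter of efficiency. The listed secondary models lose precision whether the response is a change score, a raw score, or a series with baseline as a visit level. On the better-supported readings (change score or visit level), the covariate would cut single-visit variance by 10 to 35% over r = 0.8 down to 0.3. On the raw-score reading the cut would be 9 to 64% over r = 0.3 up to 0.8.

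These sizes rest on assumed correlations, equal variances and complete data. The planned analysis is valid but less precise than the collected data allow, and the direction of any imbalance error depends on a choice of response that section 2.9.3 does not state. The omission is definite for the listed terms and less certain for what will finally be fitted. The point is confined to the four questionnaires.

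**What to change.** Add to section 2.9.3: each secondary LMM for K-BDI-II, EQ-5D-5L index, EQ VAS, SRI-SF, STAI-state and STAI-trait will model the post-baseline visits and include the participant's Visit 1 value of that outcome, taken before randomisation, as a covariate.

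Naming Visit 1 settles which of the two K-BDI-II values is the baseline. Requiring it before randomisation matters because Table 1 places both at the same visit, in an unblinded trial. PGIC has no baseline and stays outside the change, as do the biosignals.

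The cost is one sentence and one degree of freedom per model, with no new data. It should be fixed before any group comparison is seen, so that the covariate cannot look chosen from the results.
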